## Abstract

**Background:**

Parkinson’s disease (PD) is a neurodegenerative disorder characterized by progressive motor deficits and gait disturbances. While medication offers symptomatic relief, long-term complications and gradual functional decline remain significant challenges. Robot-assisted training provides intensive, task-specific motor rehabilitation and has shown promise in improving gait for PD patients. Soft wearable robot suits, designed with lightweight, flexible materials, offer enhanced comfort, adaptability, and biomechanical support compared to traditional robots. However, there is limited evidence regarding the effectiveness of hip extensor assistance with soft wearable robots for gait improvement in PD.

**Methods:**

This is a prospective, single-center, single-blind, parallel-group study, and will recruit 34 PD patients. The participants will be assigned to either a robot or control group. Both groups will receive identical rehabilitation interventions, each session comprising 20-min of strength training, 5-min rest, and 20-min of treadmill walking. The rehabilitation program will be applied identically to all participants. The key difference between the groups will be whether participants wear the soft wearable robot suit during treadmill walking session. The intervention will be conducted 2 times per week, a total of 12 sessions for 6 weeks. The H-Medi (HUROTICS, Inc.), a cable-driven soft wearable robot suit will be utilized for the intervention and hip extensor assistance will be applied. For outcome measures, the following assessments will be performed at baseline (T0) and post-intervention (T1): Gait speed, Timed-Up and Go test, Short Physical Performance Battery, Berg Balance Scale, Movement Disorder Society-Unified Parkinson’s Disease Rating Scale, Freezing of Gait Questionnaire, gait parameters, muscle strength and endurance, quadriceps muscle thickness, body composition, cognition, and depression. The primary outcome will be the difference of gait speed from T0 to T1. The secondary outcomes will be the differences of other measures.

**Discussion:**

This study will be the first to assess hip extensor assistance provided by a soft wearable robot suit as a targeted therapy for gait impairment in PD. Results are expected to clarify device usability, safety, and impact on gait. By focusing on hip extension, the findings may help advance personalized gait rehabilitation and inform the design and clinical adoption of future wearable robotic devices for PD.

**Clinical trial registration:**

KCT0010793.

## Introduction

### Background and rationale

Parkinson’s disease (PD) is one of the most common neurodegenerative disorders, marked by the progressive degeneration of dopaminergic neurons in the substantia nigra and the resulting dopamine deficiency (1). PD is clinically characterized by the presence of bradykinesia in combination with either resting tremor, rigidity, or both, and is frequently accompanied by non-motor symptoms such as cognitive decline, depression, sleep disturbances, and autonomic dysfunction (2). Reduced motor function caused by dopaminergic deficits leads to impaired motor automaticity, which ultimately results in gait disturbances and adversely affects the quality of life in patients with PD (3). Although dopaminergic pharmacotherapy remains the gold standard of treatment, it offers only symptomatic relief and is associated with long-term complications such as levodopa-induced dyskinesia. Surgical interventions, including deep brain stimulation, provide benefit for selected individuals, yet most patients experience gradual functional deterioration despite therapy. The global prevalence of PD is rising significantly, mainly driven by population aging, increased disease duration (4–6). Therefore, there is a need for disease-modifying treatments and integrated rehabilitative strategies to preserve motor function, including gait, and to improve quality of life in patients with PD.

Robot-assisted training has recently emerged as a promising rehabilitation technology designed to deliver intensive, repetitive, and task-specific motor training to improve motor function, mobility, and gait restoration (7). One of the well-established pathophysiological goals of utilizing robot-assisted training to improve motor function is to promote neuroplasticity; therefore, it is widely used for diseases affecting the central nervous system, such as PD or stroke (7, 8). Robotic devices can assist or resist movements as needed, ensure consistent training intensity and dosage, and provide real-time feedback, thereby enhancing physical performance and motivation compared to conventional rehabilitation conducted by physical therapists (9). These benefits may arise from the ability to deliver high-repetition, task-specific, and precisely controlled interventions, reduce therapist burden, support patient engagement through individualized programming, and provide reliable, objective monitoring features that conventional therapy may lack due to variability in manual guidance and therapist workload. Traditionally, robots are primarily categorized into two types, exoskeletal and end-effector robots. However, several limitations restrict their broader adoption and clinical impact. Exoskeletal robots are often characterized by their weight, mechanical complexity, and high cost, which can make achieving a comfortable and precise fit challenging across diverse users (10). Misalignment between the axes of robotic joints and the wearer’s anatomical joints can induce unintended forces and torques, leading to discomfort, potential safety hazards, and even long-term injury with frequent use. Moreover, these devices generally lack portability due to their bulk and design complexity, restricting their practical application primarily to controlled, specialized clinical or research environments (11). End-effector robots, while generally simpler and safer regarding alignment, are limited in their ability to isolate control of individual joints and may lead to less natural movement patterns, offering insufficient support for patients with severe motor deficits (12).

To address the limitations of exoskeletal and end-effector robots, there is a growing need for the development and implementation of soft wearable robots in clinical rehabilitation. Soft wearable robots are designed using flexible, lightweight materials that conform closely and naturally to the human body, thereby addressing key limitations of traditional rigid robotic systems, including excessive weight, mechanical complexity, poor fit, and limited portability (13). By reducing overall weight and mechanical complexity, these devices may provide a more natural and comfortable interface between the user and the device, enabling flexible and personalized assistance. In addition, soft wearable robots utilize flexible, lightweight materials and cable-driven actuation systems, such as Bowden cables, to transmit mechanical assistance efficiently while allowing free and natural joint motion. This design minimizes interference with voluntary movement, which is particularly critical for patients with PD, who often experience impaired motor automaticity and fluctuations in gait initiation and rhythm, including freezing of gait (FoG). FoG, characterized by a temporary inability to step forward despite the intention to walk, is a major contributor to falls, imbalance and reduced mobility in PD (14). It is well known that external cues can help overcome impaired gait function by providing additional sensory input that facilitates the activation of locomotor networks and restores step rhythm (15, 16). In this context, soft wearable robots can serve not only as physical assistive devices but also as sources of external cueing through synchronized mechanical assistance and sensory feedback. Equipped with sensors such as inertial measurement units (IMU), these robots can detect gait phases in real time and deliver timely hip assistance aligned with the user’s walking cycle (17, 18). Through the combined effects of mechanical aid and external cueing, soft wearable robots have the potential to promote smoother, more stable, and energy-efficient gait patterns in patients with PD.

Recently, robot-assisted training has become increasingly utilized for patients with PD to address motor impairments, including gait dysfunction. Current applications of robot-assisted training in patients with PD have focused on improving key gait parameters (9, 19). Picelli et al. have reported robot-assisted gait training showed significant effects on 10-meter walk test, stride length, cadence, balance, and Movement Disorder Society-Unified Parkinson’s Disease Rating Scale (MDS-UPDRS) Part III (20–23). Sale et al. and Furnari et al. also showed similar results (24, 25). A recent systematic review and meta-analysis also highlighted the benefits of robot-assisted training in improving outcomes such as the Berg Balance Scale (BBS), Activities-specific Balance Confidence Scale, 10-meter walk test, gait speed, stride length, cadence, and MDS-UPDRS Part III. However, the overall level of evidence was low. Additionally, the Timed Up and Go test (TUG) and the 6-min walk test were assessed, with findings indicating a very low level of evidence (9).

Additionally, studies employing soft wearable robots are increasingly being reported. Previous research on soft wearable robotic suits for gait assistance has primarily focused on providing hip flexor or extensor support to improve mobility in diverse populations, including healthy older adults and patients undergoing rehabilitation after neurological conditions These studies have demonstrated that such devices can reduce muscular effort, enhance joint kinematics, and improve gait efficiency and symmetry by augmenting hip flexion and/or extension during walking (26–28). Despite these promising results, the application of soft wearable robotic suits specifically targeting hip flexor or extensor assistance in patients with PD remains limited. Kim et al. described the potential of soft wearable robotic apparel that provides hip flexion assistance to mitigate FoG in an individual with PD (29). A randomized control study conducted by Kawashima et al. also utilized a wearable robot that assists hip flexion and extension to improve gait function. Although the robot group showed improvements in distance and gait speed during the 3-min walk test, these changes were not statistically significant compared with the control group (30). PD presents distinct gait impairments, including reduced hip extension during the stance phase, which contributes to decreased stride length and mobility limitations (31). Unlike previous study that employed robotic devices assisting both hip flexion and extension, this study will focus solely on hip extensor assistance. This targeted approach is based on the biomechanical understanding that enhancing hip extension can more effectively improve propulsion during walking. We hypothesize that by specifically augmenting the impaired hip extensor function characteristic of PD gait, the robotic device will enhance hip extension, thereby promoting greater propulsion, increased stride length, improved stability, and overall enhancement of gait mechanics (32, 33). In addition, we suggest that these improvements in gait could be further facilitated and consolidated through neuroplasticity (7, 34). Ultimately, this focused assistance may lead to enhanced mobility and more efficient walking in patients with PD.

Therefore, this study aimed to evaluate the impact of a soft wearable robotic suit with hip extensor assistance on gait in patients with PD.

## Methods

### Trial design

This is a prospective, single-center, single-blind, parallel-group trial. Participants will be assigned to two groups, in a 1:1 ratio: the robot group and the control group. The intervention session times will be pre-assigned as either robot or control sessions, with an equal number of slots for each group. Participants will then select their preferred session time according to their personal schedules, without knowing which sessions are designated as robot or control. Their group allocation will be determined based on this selection. As randomization is not employed and group assignment is based on self-selection, potential selection bias and confounding may occur. However, since session times for both groups are evenly distributed and baseline demographic and clinical characteristics of participants will be collected, we suggest that potential bias can be minimized. In the analysis of study results, we will apply appropriate statistical adjustments for any baseline differences. One research investigator will manage the session schedule and contact participants. This investigator, physical therapists conducting the intervention, and the participants will not be blinded to group assignments. All other investigators including outcome assessors, investigators involved in data interpretation and analyses, and the principal investigator (PI) will remain blinded throughout the study. Group assignments will be unblinded only after completion of the final statistical analyses, or during the study if a serious adverse event occurs, with the approval of the PI.

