### Statistical methods

Demographic and clinical characteristics will be summarized using frequencies and percentages for categorical variables and means with standard deviations (SD) for continuous variables. The Shapiro–Wilk test will be used to assess the normality of continuous variables. To compare baseline characteristics between the intervention and control groups, an independent t-test will be applied for normally distributed variables, while the Mann–Whitney U test will be used for non-normally distributed variables.

All participants who undergo the intervention will be included in the intention-to-treat (ITT) population, which will also serve as the basis for safety analyses. Participants in the ITT population who complete both baseline and post-intervention assessments will comprise the full analysis set (FAS). Efficacy analyses will be conducted based on the FAS.

For efficacy analyses, the normality of outcome variables will be assessed using the Shapiro–Wilk test. Baseline characteristics will be included as covariates for adjustment in the statistical models. Additionally, comparisons between the robot (intervention) and control groups under each condition will be performed using either the independent t-test or the Mann–Whitney U test, depending on the distribution of the data. To compare post-intervention outcomes between the groups while adjusting for baseline values, analysis of covariance (ANCOVA) will be used. The post-intervention measurement will be the dependent variable, group assignment the independent factor, and the baseline measurement of the outcome will be included as a covariate. This approach accounts for any baseline imbalances and increases statistical power. Assumptions of normality and homogeneity of regression slopes will be assessed prior to analysis. Statistical significance will be set at a two-sided *p*-value of <0.05 for all analyses.

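### The adjustment for conceded confounding rests on three unreconciled statements, and the one model written out adjusts only for the baseline outcome

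*Protocol article*

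**What the plan says.** Trial design states the problem itself: "As randomization is not employed and group assignment is based on self-selection, potential selection bias and confounding may occur". Participants pick a slot "without knowing which sessions are designated as robot or control", and the slot fixes the arm. The analytic remedy offered there is that "we will apply appropriate statistical adjustments for any baseline differences". It names no variables and no criterion.

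Statistical methods then says several things:

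- Baseline comparison of the arms is by significance test: "To compare baseline characteristics between the intervention and control groups, an independent t-test will be applied" when the variable is normally distributed, and a Mann-Whitney test otherwise.
- For efficacy, "Baseline characteristics will be included as covariates for adjustment in the statistical models". The characteristics are not named, and neither are the models.
- Unadjusted t-tests or Mann-Whitney tests of the arms are also planned.
- One ANCOVA is written out. The post-intervention value is the response, with "group assignment the independent factor, and the baseline measurement of the outcome will be included as a covariate". The text goes on to say that this takes care of any imbalance at baseline.

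No sentence says which of these is the primary analysis of gait speed.

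**The concern.** In a non-randomised comparison the covariate set carries much of the causal claim, so the protocol should point to one model. As worded, a reader could fit an unadjusted test, an ANCOVA on baseline gait speed alone, an ANCOVA with an open-ended set of baseline characteristics, or an ANCOVA whose covariates depend on what turned out to differ. These can give different answers with about 27 people.

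Two specific harms follow. If the written-out ANCOVA is used alone, a measured prognostic factor that is linked to choice of session time, and is not captured by baseline gait speed, stays in the treatment effect. If covariates are chosen after looking at the baseline table, the model depends on the data, and modest but relevant imbalances are likely to be passed over.

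**Working it through.** **Inputs from the protocol.** Sample size: 17 per arm, 34 in total, 80% follow-up, δ = 0.18, σ = 0.17. Statistical methods: two-sided 5% tests, with efficacy analysed in those who have both assessments. Expected completers: 34 × 0.8 = 27.2, so 27 to 28, or about 14 per arm.

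**Assumptions, not in the protocol.** The true imbalance d in a confounder X is 0.3 to 0.8 SD. X shifts the outcome by b = 0.3 or 0.5 outcome SD per SD of X. X is unrelated to the baseline outcome.

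**The plan's own figure.** Lehr's formula gives 16/(0.18/0.17)² = 14.27 per arm, and 14.27/0.8 = 17.84. The plan states 17. The gap does not matter here, and 17 is used below.

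**1. What the written-out ANCOVA leaves behind.** Under these assumptions its bias is b × d outcome SD. A simulation (20,000 runs, 17 per arm, no true effect, baseline-outcome coefficient 0.6) agrees:

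| d | b | b × d | Simulated bias, baseline outcome only | Type I error | Bias with X added | Type I error |
|---|---|---|---|---|---|---|
| 0.5 | 0.3 | 0.15 | 0.153 | 8.3% | 0.003 | 5.0% |
| 0.5 | 0.5 | 0.25 | 0.253 | 13.7% | 0.002 | 5.0% |
| 0.8 | 0.5 | 0.40 | 0.398 | 28.7% | −0.002 | 5.1% |

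If σ = 0.17 is taken as the outcome SD (a further assumption), the d = 0.5 rows give 0.15 × 0.17 = 0.026 and 0.25 × 0.17 = 0.043. Those are 14% and 24% of δ = 0.18. Where X is correlated with baseline gait speed, the ANCOVA removes the shared part and the bias is smaller.

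**2. A rule that waits for differences, if that means p<0.05.** Power of the baseline t-test uses the noncentral t distribution with 2n − 2 degrees of freedom and noncentrality d√(n/2). For n = 17 and d = 0.5, the noncentrality is 0.5 × √8.5 = 1.46.

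| True imbalance | Flagged, 17 per arm | Flagged, 14 per arm |
|---|---|---|
| 0.3 SD | 14% | 12% |
| 0.5 SD | 29% | 25% |
| 0.8 SD | 62% | 53% |
| 1.0 SD | 81% | 72% |

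An observed difference reaches p<0.05 only from 0.70 SD (17 per arm) or 0.78 SD (14 per arm). Power passes 50% at a true imbalance of about 0.69 SD or 0.77 SD.

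In the same simulation, the share of X's bias that survives this rule at 17 per arm is about 63% (d = 0.3), 48–49% (d = 0.5) and 22% (d = 0.8). At 14 per arm it is 65–66%, 52–54% and 29%. Type I error under the rule is 4.6–7.1%. Always adjusting for X gives 4.9–5.4%.

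**3. Chance selection.** With no true imbalance, the probability that at least one of k independent baseline variables is flagged is 1 − 0.95^k. That is 23% for k = 5, 40% for k = 10 and 64% for k = 20.

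**4. Price of covariates.** With p covariates besides arm, the treatment-effect variance is multiplied on average by about (N − 3)/(N − 3 − p), before any gain from explained outcome variance. For N = 27:

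- p = 1: 24/23 = 1.04
- p = 3: 24/21 = 1.14
- p = 10: 24/14 = 1.71

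Going from one covariate to three therefore costs a factor of 23/21 = 1.095 in variance, or about 5% in standard error. An open-ended list could cost far more. The figure of ten is only an illustration, since the protocol gives no number.

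**The case against.** The covariate sentences in Statistical methods can be read together: an ANCOVA with the baseline outcome plus baseline characteristics, which would carry out the promise in Trial design. The text does not say that the baseline outcome is the sole covariate. A covariate list is also commonly left to an analysis plan, which is not shown, so its absence is no fault. This reading is possible, but the text does not settle on it. The promise in Trial design depends on differences, the covariate sentence does not, and the ANCOVA is spelled out with one covariate and then credited with dealing with all imbalance. That credit is wrong on any reading of the model as written.

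Four stronger readings are tempting and are not supported:

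- *Covariates will be picked by significance tests.* The protocol plans baseline tests but never links them to covariate selection. The p<0.05 trigger is an inference.
- *Such a rule misses most confounding.* That holds only for true imbalances below about 0.7 SD. In the simulation the rule still removed between about 34% (100 − 66) and 78% (100 − 22) of a measured confounder's bias.
- *Such a rule badly inflates type I error.* It stayed at 4.6–7.1%. The larger inflation in the first table belongs to leaving X out altogether.
- *Adjustment is the plan's only defence.* Slots are chosen without knowledge of the arm, their numbers are balanced, and outcome assessors and analysts are blinded. Blind choice limits confounding to factors tied to preferred session time.

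**Conclusion.** The point stands as an unreconciled adjustment plan together with one incorrect statement. The protocol concedes confounding, gives three adjustment statements that do not fix one model, names no primary model for gait speed, and overstates what the baseline-outcome ANCOVA does.

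The size depends on assumptions that the protocol cannot supply. For a 0.5 SD imbalance in a confounder unrelated to baseline gait speed, the written-out ANCOVA leaves a bias of 0.15 to 0.25 outcome SD, and adding the confounder brings it to about zero. A difference-triggered rule, if it means p<0.05, would leave about half of that bias. The main harm is residual bias and an undetermined model. The protocol should be corrected before analysis. No covariate model deals with confounders that were not measured.

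**What to change.** - State one primary ANCOVA for gait speed: post-intervention gait speed on arm, baseline gait speed, age and baseline MDS-UPDRS Part III (or Hoehn and Yahr stage), entered whatever the observed baseline differences.
- Label the unadjusted tests and any other covariate sets as sensitivity analyses.
- Describe baseline balance with standardised differences, and say that p-values will not be used to select covariates.
- Replace the promise in Trial design with a reference to this model, and correct the claim about the ANCOVA to say that it covers the baseline value of the outcome only.
- Use session time only in a sensitivity analysis, in broad bands that each contain both arms. The slot determines the arm, so finer coding would be collinear with treatment.

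The cost is a few sentences and about 2 further degrees of freedom with 27 to 28 completers, roughly 5% in standard error before any gain from prognostic covariates. No new data should be needed: MDS-UPDRS is scheduled at baseline, stage is an entry criterion, and baseline demographics are collected (age is assumed to be among them). Unmeasured confounding remains and should be stated as a limitation.
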